### Sample

Patients are eligible for the trial if: their primary problem is non-suicidal, non-psychotic, unipolar mood disorder, such as depression or dysthymia or mixed anxiety and depressive disorder based on ICD-10 criteria
[30]; they sign a written consent form for screening and for treatment; they are registered with a GP within the local area and they are at least 18 years old. There is no upper cut-off for severity of depression or anxiety symptoms and participants can have comorbid physical and mental health problems and receive concurrent treatments. Referrals are only excluded if they have: high current risk of suicide (current suicide plans and intent to kill themselves); current psychotic symptoms (due to schizophrenia or bipolar affective disorder or severe depression with psychotic features); current substance abuse/misuse (severe dependency on alcohol, illicit drugs or tranquilisers) or cognitive impairment that impedes the use of a computer.

### Recruitment

Health professionals working in primary care, or in the voluntary sector, signpost patients to the study by handing them an envelope containing a patient information sheet, a consent form and a self-referral questionnaire. People who find out about the study through public advertisement can also contact the research team directly by telephone or email, or can download the study entry documents from a designated website. Patients are encouraged to email or telephone the research team before completing and posting the self-referral questionnaire and consent form, should they have any questions or if they wish to discuss something confidential.

### Assessment

On receiving a completed self-referral questionnaire and consent form, the study’s research associate (JM) assigns a unique trial identifier number to the patient and copies their self-referral questionnaire twice after masking any identifiable patient details. The anonymised copies of the self-referral questionnaire are distributed to the study’s assistant (KB) and to two expert clinicians (NR, GT). They all independently read the self-referral questionnaire, and record their judgment on the patient’s diagnosis and suitability for cCBT. The research associate (JM) invites the patient for a brief (15 to 30 minutes) telephone interview to determine their eligibility for study entry and to discuss any questions they may have about the study. If a patient is not eligible, the research associate (JM) discusses this with them, suggests alternative avenues for help, and records the reasons for ineligibility in a web-based database.

### Treatment allocation

Patients eligible for trial entry receive a treatment consent form and a set of blank standardised self-report questionnaires (baseline assessments) to complete and post to the research team in a stamped addressed envelope. On receiving the completed treatment consent form and baseline assessments, the research associate (JM) randomises patients into one of the four study intervention groups using a web-based system set up by the Clinical Research Trials Unit (CRTU) of the Norfolk & Norwich University Hospitals (NNUH) Trust. The system follows a block-randomisation: for every 32 referrals, it ensures that eight patients are assigned to each of the four arms of the trial so that the clinician and assistant who offer phone support to patients have similar workload distribution over time. Figure
1 is a CONSORT diagram
[31] of the randomisation and flow of participants through the study. 

**Figure 1 F1:**
[figure not shown]
CONSORT* diagram of participant flow (*according to Schulz KF, AltmanDG, Moher D, the CONSORT Group, 2010).

### Interventions

After randomisation, the research associate (JM) emails or telephones the patient with an access code for logging into the cCBT system and with the details of the person who will be supporting them. Patients are registered with the system as active participants once they log in for the first time and choose their own password. The support person emails or telephones the patient within a week of randomiation to introduce themselves and schedule their support sessions. All patients are offered an intervention with two components, cCBT and some type of adjunct telephone support.

### cCBT

The computerised cCBT system used in this study is Beating the Blues (BtB) marketed by Ultrasis Ltd based in London, UK. This was chosen because at the time of the study set-up it was the cCBT system recommended in the UK by the National Institute for Clinical Excellence (NICE)
[3] and the Department of Health (DH)
[32] as an effective and cost-effective treatment method for mild-moderate depression in primary care. During eight 50-minute sessions, BtB uses text, videos, voice instructions, diagrams and pictures to teach patients how to identify unhelpful thoughts and come up with helpful alternatives, and how to perform activity scheduling, problem-solving and other relevant homework tasks between their computer sessions. Each computer session builds on the one before and its completion triggers printing of a progress report.

Most patients use the computerised therapy system from home; those who do not have access to a computer, or who wish to use the system outside their home environment, can access the cCBT system in public places such as libraries, community centres or Internet cafes and are reimbursed for their expenses. Patients go through BtB at their own pace, but it is suggested that they cover a module per week, allowing enough time in-between sessions for homework (for example, rehearsing practical tasks or keeping diaries), with the aim of completing the whole programme within 12 weeks.

#### Telephone support

Individual support is given as a scheduled, telephone call on average once a week or fortnight (depending on how fast the patient goes through the programme) for 3 months or longer, and up to 6 months if needed. Support sessions are either brief (5 to 10 minutes per call) or extended (20 to 30 minutes per call). Patients can receive up to 12 telephone calls over 12 to 24 weeks, so they have a maximum of 1 to 2 hrs of brief support or 4 to 6 hrs of extended support throughout using the cCBT system. *Ad-hoc* contact is also available, in case patients raise risk issues or get stuck with the system.

Both brief and extended support sessions focus on monitoring patient progress and mental state as necessary. Extended support sessions offer additional therapy advice by elaborating on some of the treatment techniques described in the cCBT system (for example, to help patients identify thinking errors and alternative beliefs, problem-solving difficulties with doing homework, etcetera). Support is not standardised, so that it can be tailored to individual patients’ needs and preferences.

Support sessions are offered either by a clinician (JT), a PhD nurse with CBT clinical qualifications and 20 years clinical experience, or by an assistant (KB), a graduate psychologist with no clinical qualifications but with 2 years experience of working with people with depression and anxiety in a voluntary organisation. Both members of staff receive individual telephone or face-to-face clinical supervision from a senior CBT-trained Clinical Psychologist (NR) and research supervision from the Chief Investigator (LG).

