### Sample size

Sample size calculations are based on a between-group comparison of post-treatment scores at 12-weeks follow-up post-randomisation on our primary outcome measure (WSAS), assuming a significance level of 0.05 with a standard deviation of 8.5 for that measure; this standard deviation was taken from Proudfoot *et al*.
[6], whose study used the same intervention, outcome measure and follow-up interval.

A sample size of 35 per group (total 140 patients) is sufficient to detect main effects (brief vs. extended, and clinician vs. assistant) of 0.477 standard deviations (about 4.1 points) in our primary outcome measure with 80% power, or of 0.522 (about 4.4 points) in our primary outcome measures with 90% power. The estimated sample size of 140 patients with available data can detect an interaction effect (for example, the difference between brief and enhanced, compared between clinician and assistant) of about 0.961 standard deviations (about 8.2 points) on our primary outcome measure with 80% power.

Allowing for a 30% drop-out rate, we intend to randomise 50 patients in each of the four groups (total 200 randomised patients). We estimate that about a third of all screened patients may be unsuitable for the trial or refuse participation (based on a similar pragmatic trial by Marks *et al*.
[48]), therefore to achieve 200 randomised patients we aim to recruit a total of 300 referrals.

Our sample size calculation and effect estimates are conservative. Our hope is that adjustment by the corresponding baseline outcome measure reduces the standard error of the effect estimates and hence increases the power for a given sample size.

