### Economic evaluation

To establish the cost-effectiveness of clinicians vs. assistants offering brief vs. extended support, we will combine the effects and costs of each of the four support modes (brief-clinician vs. brief-assistant vs. extended-clinician vs. extended-assistant support). Effects will be measured using both the WSAS and the EQ-5D. Cost will be estimated by assigning appropriate unit costs to resources used by patients (therapist contact time, cCBT use, medication use, GP consultations, in-patient and out-patient care, etcetera) before, during and after the interventions. All costs will be calculated in UK £ Sterling using both internal sources (for example, the relevant local organisations’ finance departments) and external sources (for example, Personal Social Services Research Unit (PSSRU)-health and social care costs
[53]). We will estimate cost-effectiveness from the perspective of the NHS and social services according to NICE guidelines
[41]) and also from a broader societal perspective (encompassing for example, patient travel costs, lost productivity and other support received).

If one support mode is shown to be less costly and more effective than all others, determining the most cost-effective support mode will be straightforward, as that support mode would dominate others. Alternatively, the incremental cost per unit of effect will be estimated for each support mode, and the resulting incremental cost-effectiveness ratio (ICER) will be assessed in relation to a range of cost-effectiveness thresholds. To characterise the level of uncertainty in decision-making based on the cost-effectiveness analysis, we will present economic data based on the cost-effectiveness acceptability curve (CEAC) and cost-effectiveness acceptability frontier (CEAF)
[54].

Additionally, sub-group analysis (severe vs. mild/moderate depression or anxiety; referrals from GPs vs. mental health professionals) will be conducted in order to assess how the costs and effects of different modes of support for cCBT vary across different patient groups. Sensitivity analysis will assess the robustness of conclusions to key assumptions that are made within the economics analysis (for example, the level of payment for clinicians or assistants employed). Finally, we will estimate the budgetary impact for the NHS of the population-wide long-term implementation of the most cost-effective mode of individualised support for cCBT.

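### One clinician and one assistant deliver all the support, so the stated power for clinician versus assistant applies to those two people and does not extend to staff grade

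*Protocol article*

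**What the plan says.** **Who delivers support.** Telephone support describes the two providers: "a PhD nurse with CBT clinical qualifications and 20 years clinical experience, or by an assistant", who has no clinical qualifications and two years' relevant experience. Treatment allocation confirms that there is one of each, since the blocks of 32 are chosen "so that the clinician and assistant who offer phone support to patients have similar workload distribution over time". The other clinicians in the article rate referral questionnaires or supervise. The Design section has each provider giving both brief and extended support.

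**What is claimed.** Under Sample size, 140 analysed patients are "sufficient to detect main effects (brief vs. extended, and clinician vs. assistant"), with the same detectable effect for both factors. Methodological considerations repeats that the sample is adequate for both contrasts. Statistical analysis plans linear models for the two main effects.

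**What the result is for.** The primary objectives in the Background compare clinician with assistant support on outcomes, cost-effectiveness and acceptability. Economic evaluation will "estimate the budgetary impact for the NHS of the population-wide long-term implementation" of the most cost-effective mode. Potential implications looks ahead to advice on the mix of staff expertise.

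**What is not said.** Methodological considerations discusses the limited power for the interaction. The article nowhere notes that each level of the staff factor is one person.

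**The concern.** Patients are randomised between two people, and the two people stand for two grades. Any stable difference between them, in manner, skill or rapport, adds to the clinician-versus-assistant difference and cannot be told apart from it. Profession and years of experience are aliased with the person in the same way. No analysis of these data can undo this, because there is one provider per level and no degrees of freedom for variation between providers.

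The patient-level standard error reflects variation between patients only. It is the right measure of uncertainty for whether these two providers differ. It is too small for whether clinicians and assistants differ, if providers within a grade vary at all. A chance difference between two individuals could then be read as the value, or lack of value, of clinical training and passed into a staffing recommendation.

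**Working it through.** **Inputs from the Sample size section.** The calculation is made "assuming a significance level of 0.05 with a standard deviation of 8.5 for that measure". "A sample size of 35 per group (total 140 patients) is sufficient to detect main effects", that is 70 versus 70 for each factor. The smaller of the two effects is given as one "of 0.477 standard deviations (about 4.1 points) in our primary outcome measure with 80% power". The larger effect, which the section pairs with the higher power, is worded "or of 0.522 (about 4.4 points) in our primary outcome measures with 90% power".

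**Assumed input.** The between-provider ICC is not given. I use 0.01, 0.02 and 0.05, the same in both grades, with 8.5 as the total SD.

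**Step 1: the plan's own figures (two-sided 0.05).**
- SE in SD units = √(2/70) = 0.169; in points, 8.5 × 0.169 = 1.44. Half-width = 1.96 × 1.44 = 2.8 points.
- Power at 0.477 SD = Φ(0.477/0.169 − 1.96) = 80.6%; with the noncentral t, 80.0%. The stated 80% is reproduced.
- Power at 0.522 SD = Φ(0.522/0.169 − 1.96) = 87.0%; with the noncentral t, 86.6%. The stated 90% is not reproduced; 90% needs about 0.552 SD.
- Interaction of 0.961 SD: SE = √(4/35) = 0.338, power = Φ(0.961/0.338 − 1.96) = 81%. The stated 80% is reproduced.

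**Step 2: inference to staff grade, one provider per level.**
- Variance of the difference = (2/70) × 8.5² × (1 + 69 × ICC).
- Half-width = 1.96 × the square root of that variance.
- Power at 0.477 SD = Φ(0.477 / √[(2/70)(1 + 69 × ICC)] − 1.96).
- Type I error of the planned patient-level test = 2 × [1 − Φ(1.96/R)], where R = √[(1 + 69 × ICC)/(1 − ICC)]. This is how often the test rejects when the grades do not differ on average.

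| Assumed ICC | 1 + 69 × ICC | SE (points) | 95% half-width (points) | Power at 0.477 SD | Type I error |
|---|---|---|---|---|---|
| 0 | 1.00 | 1.44 | 2.8 | 81% | 5% |
| 0.01 | 1.69 | 1.87 | 3.7 | 58% | 13% |
| 0.02 | 2.38 | 2.22 | 4.3 | 45% | 21% |
| 0.05 | 4.45 | 3.03 | 5.9 | 27% | 37% |

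Worked line for 0.01: SE = 1.44 × √1.69 = 1.87; half-width = 1.96 × 1.87 = 3.7; power = Φ(0.477/0.220 − 1.96) = Φ(0.21) = 58%; R = √(1.69/0.99) = 1.307, so type I error = 2 × [1 − Φ(1.50)] = 13%.

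**Step 3: would more patients help?** With unlimited patients the variance tends to 2 × ICC × 8.5². The smallest effect detectable with 80% power then stays at (1.96 + 0.84) × 8.5 × √(2 × ICC): about 3.4 points at ICC 0.01 and 7.5 points at ICC 0.05, against the target of about 4.1.

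The figures in steps 2 and 3 treat the ICC as known. They flatter the design, because these data cannot estimate it.

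**Step 4: the other contrasts.** Each provider gives both durations, so a provider's overall effect cancels from brief versus extended. Variation in how providers differ between durations does not cancel. The interaction is a contrast between the same two people and is as specific to them as the staff effect.

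**The case against.** The strongest reply is that nothing in the Sample size section is miscalculated on this ground. The 80% figure reproduces, and the planned analysis is valid for the two providers studied, so the issue is how far the result carries. That stands. A reader might infer that the stated 80% power is simply wrong; the article does not support this, because the figure fails only for inference to grade and only if the ICC is above 0.

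The size of the loss also rests wholly on assumed ICCs. That stands too: at ICC 0 nothing changes. The aliasing itself needs no assumption.

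A reader might also take the statement that support is not standardised as evidence of large provider effects. The article ties it to tailoring for individual patients, so that is inference. Other features may limit or help describe provider differences: a common eight-session programme, a shared clinical supervisor, taped sessions for fidelity, and a planned qualitative comparison of content and style. None of them separates grade from person.

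Finally, the NHS-wide estimate carries forward the best of four modes, so it depends on duration as well as staff. Its sensitivity analysis is open-ended, with pay level only an example, and Potential implications is worded cautiously. This narrows the economic point to choices that turn on clinician versus assistant, but does not remove it.

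**Conclusion.** The concern holds as a limit on inference. Staff grade and individual are fully aliased, which is certain from the text, while the objectives and planned uses concern staff grade and the limit is not acknowledged. The article's 80% power is correct for these two people. For staff grade, the table in the working gives the loss over assumed ICCs of 0.01 to 0.05: power between about 58% and 27%, type I error between about 13% and 37%, and intervals about 1.3 to 2.1 times as wide (3.7/2.8 and 5.9/2.8). These rest on a normal approximation and a common, known ICC.

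Two further readings should be resisted. The NHS budget impact does not fall as a whole; it is affected where the chosen mode depends on who gives the support. Nor is brief versus extended wholly safe: it escapes the aliasing, but the same two people deliver it, so its power should not be called fully generalisable.

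**What to change.** - In Sample size and Methodological considerations, state that the power for clinician versus assistant, and for the interaction, applies to these two providers only.
- Word the conclusions and any staff-mix recommendation for this factor as a comparison of this clinician with this assistant.
- Pre-specify one sensitivity table that widens the clinician-versus-assistant interval over a range of ICCs, labelled as assumed.
- Carry that uncertainty into the NHS budget impact wherever the preferred mode turns on clinician versus assistant.
- For brief versus extended, note that provider-by-duration variation remains.
- Do not carry forward the 90% power at 0.522 SD for either factor, since it gives about 87%.

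Trial status reports that recruitment has stopped, so the remedy asks for no added staff or patients. It costs some wording and one table; the downside is a weaker claim for one of the two factors.

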### Data collection

Baseline demographic and clinical characteristics are obtained by the self-referral questionnaire which is completed by patients and posted to the research team before randomization. The self-referral questionnaire has been suitably adapted for the purpose of this study from its previous validated version
[33]. The questionnaire has nine sections which elicit quantitative and narrative data about patients’ symptoms, computer literacy, lifestyle, past and present treatments including medication, and therapy goals and preferences for therapist-delivered interventions vs. computerised self-help.

Data on clinical outcomes, resource use and patient experiences are collected in two ways: both by post and electronically. Postal questionnaires are sent to patients at baseline (randomization) and then at weeks 12 (primary end-point) and 24 (follow-up) post-randomization with instructions to complete them and return to the research team. Electronic data are collected automatically by the cCBT system during each cCBT session. The timing of electronic data collection is recorded by the cCBT system but it varies according to the frequency with which patients log into it.

Narrative data are also collected during a 15 to 30 minute assessment with the patient pre-randomization, as part of support sessions by the clinician and the assistant, and during a 15 minute telephone interview, which asks about patient views and experiences of using a computerised self-help system and of having telephone support at 12-weeks post-randomization, by the study’s research associate (JM).

Below we give a detailed description of individual data collection tools and justification for their inclusion in the study. All standardised measures are self-reported and are collected independently of the staff proving telephone support; there are no observer-rated outcomes so there is no need for blinding.

#### Clinical outcomes

Work and social adjustment scale (WSAS)
[34,35]: this is a 5-item self-report questionnaire that assesses impairment of everyday functioning with scores of 0 to 40 (lower scores denote less impairment). Each item asks the patient to rate how much a particular area of their life is affected by their problem (work, social activities, private leisure activities, relationships) on a 9-point scale, where 0 represents ‘not at all’ and 8 represents ‘very severely’. This is a brief and well-validated measure that has previously been used in many studies and is part of routine data collection in the NHS Improving Access to Psychological Therapies (IAPT) Programme
[36].

We chose a generic measure of functioning instead of a symptom-specific measure for our primary outcome for three reasons: a) improved functioning is a key objective of primary care mental health services with the view of helping people return to work
[37]; b) people with depression and mixed anxiety are a heterogeneous group and c) we can establish cost-effectiveness measuring effects of functioning with both the WSAS, commonly used by clinicians, and the EQ-5D, commonly used by health economists.

Beck depression inventory (BDI)
[38]: this is a 21-item questionnaire that measures presence and severity of depression. Each item relates to a specific symptom of depression and includes four statements corresponding to scores 0, 1, 2 or 3 (higher scores, greater severity). Patients choose one of the four statements to describe the extent to which they were troubled by each symptom over the previous week. The items are then summed to obtain a total score that can range from 0 to 63 (higher total scores indicate more severe depression). Standard cut-offs are: 0 to 9, no depression; 10 to 18, mild-moderate depression; 19 to 29, moderate-severe depression and 30 to 63, severe depression.

Beck anxiety inventory (BAI)
[39]: this is a 21-item self-report questionnaire that assesses the presence and severity of anxiety. Each of its items corresponds to a common symptom of anxiety, which patients rate based on how much they were troubled by that symptom over the previous week (0, not at all; 1, mildly troubled; 2, moderately troubled and 3, severely troubled). The items are then summed to obtain a total score that can range from 0 to 63 (higher scores, greater anxiety). Common cut-off points are: 0 to 21, low anxiety; 22 to 35, moderate anxiety and over 36, severe anxiety.

Health-related quality of life - EQ-5D
[40]: this is a five-domain measure of health-related quality of life covering mobility, self-care, usual activities, pain/discomfort and anxiety/depression. Each domain has three levels and patients tick the statement that best describes their state of health at the time (no problems, 1; some/moderate problems, 2 and severe/extreme problems, 3). Responses to these five domains are converted into one of 243 different health state descriptions, which range between no problems in all five domains (11111) and severe/extreme problems in all five domains (33333). Patients also rate their overall impression of how good or bad their health state is on the day of completion using a separate scale of 0 to 100 (0 , worst imaginable health state; 100, best imaginable health state). We have selected the EQ-5D because it is commonly used to estimate quality-adjusted life years (QALYs) for the economic evaluation of health interventions
[41] and allows comparisons of the cost-effectiveness of different interventions across different conditions.

Patient health questionnaire (PHQ) - depression-9 item (PHQ-9)
[42] and generalised anxiety disorder-7 item (GAD-7)
[43]: the PHQ-9 and GAD-7 are brief validated scales to screen for the presence and severity of depression and generalised anxiety respectively, in primary care. Each of the 9 items of PHQ-9 and of the 7 items of GAD-7 describes a common symptom of depression or generalised anxiety respectively, which patients rate on a scale of 0 to 3 according to how often they have been troubled by this symptom in the previous 2 weeks (0, not at all; 1, for several days; 2, for more than half the days; 3, nearly every day). Standard cut-offs for PHQ-9 are 0 to 4, no depression; 5 to 9, mild depression; 10 to 14, moderate depression; 15 to 19 moderately severe depression, 20 to 27 severe depression. For GAD-7 the cut-offs are 0 to 4, no anxiety; 5 to 10, mild anxiety; 11 to 15, moderate anxiety; 15 to 21, severe anxiety.

The PHQ-9 and GAD-7 are subsidiary clinical outcome measures collected by post at 12 and 24 weeks post-randomization, and electronically every time patients log into the cCBT system. We have included them in the study because they are routinely used in the NHS to screen for depression and anxiety in primary care and to evaluate the effectiveness of psychological therapies nationwide
[36]. These will allow us to compare our study findings with published national outcomes on cCBT and related interventions
[44,45]. We will also test whether the PHQ-9 and GAD-7 can be as sensitive as the BDI & BAI in measuring depression and anxiety respectively but less cumbersome for patients to complete.

